### 2.1. Patients

The trial includes adults with a diagnosis of low-risk CVD with class I heart failure according to the NYHA (New York Heart Association) functional assessment criteria (24), diagnosed by the Cardiology and Rehabilitation team of the Hospital of Melilla. Patients must live in Melilla during the intervention phase, have mobile technology with an internet connection at home (including one of the following devices: desktop personal computer, laptop, tablet, or smartphone), and be able to access email or instant messaging frequently and reliably. Patients who suffered non-mild cardiac events prior to the first contact with this research, those whose pathologies are not classified as CVD, and those subjects who are not in full cognitive capacity that allows them to use new technology tools will be excluded. Patients will be excluded if they have any absolute or relative contraindications to exercise testing as per the American Heart Association guidelines [20]. Inclusion and exclusion criteria is show in Table 1.

In order to generate sufficient data for the development of this research, a sample size of (*n* = 30) patients will be recruited. The primary aims of this sample size determination is to evaluate whether the proposed intervention is feasible, safe, and effective. A larger randomized controlled trial that would have adequate power could be designed based on what was learned in this study. The strategies to achieve an adequate inclusion of participants that reach the target sample size include the multidisciplinary collaboration of the team from the Regional Hospital of Melilla (Cardiology Department, Head of the Rehabilitation Service and the Physiotherapy team). The collaborators were informed about the characteristics of the study in personal interviews and presentation. We ensured that the recruitment of patients has a socio-demographic diversity in relation to their social origin, gender, ethnicity, and education adapted to the particularities of the reference population. For the development of this research, an intentional non-probabilistic type of sampling will be used for the convenience of the study, due to the characteristics of the subjects. This trial has the approval of the Andalucía Ethics Committee with HIP version 17112020.

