## Abstract

Individual and group cardiac rehabilitation (CR) programs reduce cardiovascular morbidity and mortality by reducing recurrent events, improving risk factors, aiding compliance with drug treatment, and improving quality of life through physical activity and education. Home-based programs are equally effective in improving exercise capacity, risk factors, mortality, and health-related quality of life outcomes compared to hospital-based intervention. Cardio-telerehabilitation (CTR) programs are a supplement or an alternative to hospital rehabilitation programs providing similar benefits to usual hospital and home care. Despite this statement, implementation in the public and private healthcare environment is still scarce and limited. The main objective of this research was to evaluate the efficacy, feasibility, and adherence of a personalized eight-week mHealth telerehabilitation program in low-risk cardiac patients in the hospital of Melilla (Spain). The secondary aims were to investigate patient satisfaction, identify barriers of implementation and adverse events, and assess cost-effectiveness from a health system perspective. A study protocol for a single center prospective controlled trial was conducted at the Regional Hospital of Melilla (Spain), with a sample size of (*n* = 30) patients with a diagnosis of low-risk CVD with class I heart failure according to NYHA (New York Heart Association). Outcomes of this study, will add new evidence that could support the use of CTR in cardiac patients clinical guidelines.

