## 5. Conclusions

This pilot study is the first to examine the effect of a CTR intervention on patients with heart failure in a cardiac rehabilitation setting in the Hospital of Melilla (Spain). Efficacy, feasibility, adherence, satisfaction, and cost-effectiveness must show if this study will add more evidence in support of the use of CTR program as an effective tool in new cardiac rehabilitation programs.

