## Figures and Tables

**Figure 1 ijerph-18-04038-f001:**
[figure not shown]
Study design. Abbreviations CVD, cardiovascular disease; CTR, cardio-telerehabilitation.

**Table 1 ijerph-18-04038-t001:** Inclusion and exclusion criteria.

Inclusions Criteria	Exclusions Criteria
Adult over 18 Years old	Cognitive ability not suitable for the use of technologic tools.
Diagnosis: Ischemic heart disease in New York Heart Association (NYHA) functional class I-II with preserved global systolic function or in intermediate range (LVEF > 40%) after revascularized acute coronary syndrome.	
Lives in Melilla during the research period.	Absolute or relative contraindications to exercise testing
To have mobile technology with an internet connection at home (including one of the following devices: desktop personal computer, laptop, tablet, or smartphone)	
Ability and knowledge to access email or instant messaging	

Abbreviations LVEF, Left ventricular ejection Fraction.

**Table 2 ijerph-18-04038-t002:** Primary and secondary outcomes.

	Definition	Type
Primary Outcomes		
Biochemical	Hematies Level, Glucose, Creatine Kinase (CK), Triglycerides, Total Cholesterol, High Density Lipoprotein Cholesterol (HDL-C), Low Density Lipoprotein Cholesterol (LDL-C), Glycated Hemoglobin (HbA1c)	Clinical
Cardiac Function	Metabolic Equivalent (MET), Resting Heart Rate (RHR), Maximum Heart Rate (HRmax), Final Heart Rate (FHR), Rating Scale for Perceived Exertion (RPE), Systolic Blood Pressure (SBP), Diastolic Blood Pressure (DBP)	Clinical
Quality of Life	SF-12, EQ-5D	Self-Reported
Functional Capacity	Duke Activity Status Index (DASI)	Self-Reported
Secondary Outcomes		
Feasibility, Satisfaction and Usefulness	Telemedicine Satisfaction and usefulness Questionaire (TSUQ)	Self-Reported
Cost-Effectiveness	Direct Costs/Indirect Costs	€/Self-Reported
Adherence and Safety	Nº of sessions completed and adverse events record	Automatized App record

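### Section 2.1 and Table 1 define different trial populations (NYHA I heart failure versus NYHA I-II ischaemic disease after a revascularised coronary event), and the conclusions are worded for heart failure

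*Protocol article*

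**What the plan says.** The Abstract describes the sample as "patients with a diagnosis of low-risk CVD with class I heart failure according to NYHA". Section 2.1 says the same: "The trial includes adults with a diagnosis of low-risk CVD with class I heart failure according to the NYHA". Section 2.1 gives no LVEF threshold, does not require an ischaemic cause, and does not require an index coronary event. On diagnosis, it excludes only disease outside the CVD category.

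Section 2.1 then refers the reader to Table 1 for the inclusion and exclusion criteria. The diagnosis line in Table 1 is: "Ischemic heart disease in New York Heart Association (NYHA) functional class I-II with preserved global systolic function or in intermediate range". It adds LVEF above 40% and places the patient "after revascularized acute coronary syndrome". It lists no heart failure diagnosis.

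Among the exclusions in Section 2.1 is: "Patients who suffered non-mild cardiac events prior to the first contact with this research". Neither the meaning of non-mild nor a look-back period is given.

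Section 3 says that beneficial results will prove effectiveness in heart failure. Section 5 describes the study as examining "the effect of a CTR intervention on patients with heart failure in a cardiac rehabilitation setting".

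**The concern.** The text presents Table 1 as its own criteria, but the two differ on the diagnosis and on the NYHA range. A reader cannot tell from the article who is eligible.

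This matters more than usual in this design. Section 2.5 compares each outcome before and after the eight-week programme and reports Cohen's d so that results can be set against other studies. That comparison needs a named population. Section 2.1 describes purposive, non-probability sampling, so the written criteria are the main statement of whom the patients represent. The results are also meant to inform whether a larger trial is feasible and how to design it (Sections 2.1 and 3). If the patients were enrolled under Table 1, a conclusion worded for heart failure may describe a condition that some or all of them do not have.

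**Working it through.** The document gives no figure to reproduce and no arithmetic applies. The check compares the criteria item by item.

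| Item | Abstract and Section 2.1 | Table 1 | Result |
|---|---|---|---|
| NYHA class | I | I-II | conflict |
| Heart failure | required | not required | conflict |
| Underlying disease | any low-risk CVD | ischaemic heart disease only | conflict |
| LVEF | no criterion | above 40% | differs |
| Index event | none required | revascularised acute coronary syndrome | differs |

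**Is one set a summary of the other?** If so, one would contain the other. Two cases test this.

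1. A patient with ischaemic heart disease, NYHA II, LVEF above 40% and a revascularised acute coronary syndrome meets the Table 1 diagnosis line. The patient fails Section 2.1 on NYHA class.
2. A patient with low-risk, non-ischaemic CVD and NYHA class I heart failure meets the Section 2.1 diagnosis. The patient fails Table 1 on disease and on index event.

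Each set admits a patient whom the other refuses, so neither contains the other. Some patients could satisfy both, for example a low-risk NYHA I heart failure patient with ischaemic disease, LVEF above 40% and a revascularised event that does not count as non-mild.

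**The event exclusion.** Every Table 1 patient has had an acute coronary syndrome.

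- If that event counts as non-mild, the Section 2.1 exclusion removes every Table 1 patient.
- If it does not, the exclusion removes none of them on that ground.
- If it is judged case by case, the result lies between these two.

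The document does not say which reading applies.

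**The conclusion.** Sections 3 and 5 name heart failure. Under Section 2.1 this matches the entry criterion. Under Table 1 it does not, because no entry criterion there secures the diagnosis. With 30 patients planned, the number without heart failure could be anywhere from 0 to 30. That range is a logical bound and not an estimate.

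**The case against.** The best defence is that Section 2.1 points to Table 1, so the prose can be read as a loose summary with Table 1 governing. The stated aim speaks only of low-risk cardiac patients, and Section 3 sets the recruitment goal in terms of cardiac rehabilitation patients. This softens the point but does not remove it. NYHA I is not a summary of NYHA I-II, and if Table 1 governs, the heart failure wording in the Abstract and in Sections 2.1, 3 and 5 is left without a basis. Nor does the use of NYHA class in Table 1 bring heart failure in by itself: it grades ischaemic heart disease there, and Section 2.1 calls NYHA a functional assessment.

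It is also fair to say that a condensed article may leave the meaning of a non-mild event to the full protocol. That stands, so the missing definition is not a fault in itself. What remains is that one possible reading collides with Table 1.

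A reader might infer more than the documents support:

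- *That NYHA II patients enter an unsupervised programme.* Patients do train by video, but Sections 2.2 and 2.4 describe initial one-to-one sessions, supervision by physiotherapy and programme staff, and daily follow-up.
- *That three departments would each enrol different people.* Section 2.4 sets out one sequential pathway, with candidates identified and consented in Stage 1.
- *That Table 1 omits exclusions found in Section 2.1.* The exclusion column has blank cells that may come from text extraction, so nothing should rest on them. The exclusion of non-CVD disease creates no conflict in any case, because the Table 1 diagnosis already implies it.

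**Conclusion.** The point holds as an internal inconsistency that needs correcting. The Abstract and Section 2.1 define one population and Table 1 another; neither contains the other, and Sections 3 and 5 state the conclusion for a diagnosis that Table 1 does not require. This rests on the inclusion column of Table 1, which reads intact, and on no assumption about how sites behave.

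The event exclusion is a secondary and conditional point. A reader might infer that the two passages together leave no eligible patient. That is only the extreme reading of an undefined term, and Section 3 reports that recruitment is under way. Likewise, 30 of 30 patients without heart failure is an upper bound, and the documents do not suggest that it is the actual number. The realised effect depends on which criteria were used in practice, and the article does not say.

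**What to change.** 1. The investigators should reconcile the Abstract, Section 2.1 and Table 1 into one set of criteria with one NYHA range and one diagnosis. Which is right is for them to decide.
2. They should either define the non-mild event exclusion so that it is compatible with whatever index event is required, or remove it.
3. They should report patients already enrolled by NYHA class and by whether they meet the reconciled criteria.
4. They should change the population named in Sections 3 and 5 to the one that the reconciled criteria require.

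The cost is a protocol amendment and edits to the wording. Some enrolled patients may be flagged as outside the reconciled criteria; the documents do not allow their number to be estimated. The sample size and the pre/post comparison need not change.

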
#### 2.3.2. Secondary Explanatory Variable

Satisfaction and usefulness: The acceptance and usefulness of telemedicine applications is a prerequisite for identifying the potential clinical benefits of this technology. It is therefore important to complement this research with tools that examine patient satisfaction and perception [29]. An adaptation of the Telemedicine Satisfaction and Usefulness Questionnaire (TSUQ), whose psychometric analysis supports construct validity and internal consistency reliability, and which is available in English and Spanish, will be used [29]. The instrument used showed high reliability (Cronbach’s alpha 0.8) and evidence of validity with respect to perception in telemedicine [30]. It includes 17 questions that are assessed with a 5-point Likert subjective scale (1 totally disagree and 5 completely agree). The individual obtains scores from 17 to 85. The higher the score, the better the perception of the telerehabilitation intervention. Therefore each of the scores of the 17 variables indicated and finally the total score of the Test will be analyzed [29,30].

Analysis of the cost-effectiveness: To assess the cost-effectiveness of the telerehabilitation intervention, the international guidelines for conducting cost analyses in randomized clinical trials will be followed [31]. Such an economic analysis is based on the health sector perspective, which means that only costs corresponding to health interventions will be considered, and not related costs to the patient. Therefore, only costs related to the provision of health services will be taken into account [32].

Costs are divided into two categories of variables: firstly, costs related to clinical aspects (direct costs) and secondly, costs related to the use of the technology (indirect costs).

Direct costs: Numerical variable calculated on the basis of the number of hours of intervention and the cost of the physiotherapist according to the hourly wage in the health system in the centers where the research is carried out. It will be calculated based on the recording of the number of sessions in both groups.

Indirect costs: Numerical variable calculated based on the cost of using the technology for the telerehabilitation platform.

Adherence and safety: Participants will be advised to report and record barriers of use and any adverse event during the study. Number of sessions are automatically registered by the CTR tool.

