## 3. Results

Enrollment began in February 2021. First study results will be reported in the middle of 2021. Recruitment is currently underway. The recruitment goal is 30 cardiac rehabilitation patients. Data collection is anticipated to be complete by July 2021.

If the results confirm beneficial effects in biochemical, cardiac function, quality of live, and functional capacity, the effectiveness of the intervention will be proven in patients with heart failure. The successful delivery of the intervention, the absence of significant adverse effects, and the user satisfaction will demonstrate the feasibility of these interventions in cardiac patients.

The results of this study will determine if a larger-scale intervention is feasible. Further, this pilot study will be the first to examine the effect of CTR intervention on patients in a cardiac rehabilitation setting in Melilla (Spain). The results of this study will provide differences compared to previous research: first of all, its implementation in the autonomous city of Melilla (located on the African continent with particular demographic characteristics); secondly the use of the innovative CTR platform based on the App Physiotec; thirdly, the collection of outcomes that combine clinical, self-reported and economic data and lastly, automated treatment adherence registry.

This study will add more evidence in support of the use of CTR program as an effective tool in new cardiac rehabilitation programs.

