## 4. Discussion

Telemedicine has the promise of improving quality, increasing patient access, and reducing health care costs [34], and recent advances in telecommunications technologies have boosted the possibility of carrying out rehabilitation processes over the internet [35]. Studies have shown that telerehabilitation is effective in improving clinical outcomes in various pathologies, suggesting that increasing the intensity provided by telerehabilitation is a promising option to be offered to patients (32). This research should provide knowledge about the possibility of implementing CTR programs in the hospital environment, identifying the health resources and costs allocated to define new intervention policies in this group of patients. Unlike other studies that require software implementations in specific devices, our intervention generates few obstacles since it is available in any device that allows internet connection and that patients usually have (PC, laptop, tablet, smartphone), allowing access from any location and different devices prioritizing the use of mobile health. This contrasts with other studies that require a highly complex technological platform, software installation, and multidirectional cameras for controlled clinical control connecting the healthcare provider and the patient [36].

Technical problems (disconnection, device failures) and technological difficulties may arise in connection with the use of technology. However, staff members are available to provide technical support by phone or email, without the need to visit the patient at home to install or check any hardware. As possible adverse events, we considered the lack of improvement and positive evolution of the patient as well as the appearance of a low level of adherence. We also considered as an adverse event the performance of exercise with excessive workload. Patients will be informed of the importance of warning the health professional of any incident or setback in their recovery and their right to withdraw from participation in the research at any time.

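### The barrier data cover only digitally equipped volunteers, so they do not fully serve the implementation-barrier aim or support a feasibility conclusion for cardiac patients in general

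*Protocol article*

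**What the plan says.** Section 1 of the protocol article names efficacy, feasibility and adherence in low-risk cardiac patients at one hospital as the main aim. Identifying barriers to implementation is a secondary aim.

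Entry depends on digital access and skill. Under section 2.1 patients must "have mobile technology with an internet connection at home (including one of the following devices: desktop personal computer, laptop, tablet, or smartphone" and must "be able to access email or instant messaging frequently and reliably". Table 1 lists "Ability and knowledge to access email or instant messaging" as an inclusion criterion and "Cognitive ability not suitable for the use of technologic tools" as an exclusion. On selection, section 2.1 states that "an intentional non-probabilistic type of sampling will be used for the convenience of the study".

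The barrier data are described in two places. Section 2.3.2 says "Participants will be advised to report and record barriers of use and any adverse event during the study". Section 2.4 puts the barrier records in the daily follow-up of Stage 3, and it describes data for analysis as collected once a person has agreed to take part.

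Table 2 measures feasibility, together with satisfaction and usefulness, by the TSUQ, a questionnaire for people who have used the service. Section 3 says that successful delivery, no significant adverse effects and user satisfaction "will demonstrate the feasibility of these interventions in cardiac patients", and that the results will settle whether a larger-scale intervention is feasible.

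**The concern.** The entry rules select on part of what the trial sets out to measure. A patient with no home internet, or unable to handle messaging, is screened out before any barrier is recorded. A patient who declines because the program runs through an app leaves no record in the data described. Delivery, safety and satisfaction are all assessed after that filter.

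What is at stake is how the result is read. A short barrier list and high satisfaction among entrants would say little about how much of the hospital's low-risk cardiac population the program could reach. Section 3 would still state the result for cardiac patients and use it to decide on a larger study.

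**Working it through.** The plan gives no figure for reach or for digital eligibility, so there is nothing to reproduce. The check sets the passages side by side and then adds two simple calculations.

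**Aim, data and conclusion compared**

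| Element | Scope | Place |
|---|---|---|
| Main aim | Low-risk cardiac patients, one hospital | Section 1 |
| Barrier aim | Implementation | Section 1 |
| Entrants | Home device, internet, messaging ability, able to use technology; intentional convenience sample | Section 2.1, Table 1 |
| Barrier data | Use of the program, among those enrolled | Sections 2.3.2 and 2.4 |
| Feasibility conclusion | Cardiac patients, without restriction | Section 3 |

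The barrier aim is wider than the barrier data, and the conclusion is wider than both the stated aim and the entrants.

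**What 30 entrants can show**

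Input: n = 30 (section 2.1). The probability of seeing a barrier at least once, when a share p of entrants has it, is 1 − (1 − p)^30.

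- p = 0.05: 1 − 0.95^30 = 0.785
- p = 0.10: 1 − 0.90^30 = 0.958
- p = 0.20: 1 − 0.80^30 = 0.999

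Common barriers of use are therefore likely to appear. A barrier removed by the entry criteria has p of about 0 among entrants at baseline. Its chance of being seen is about 0 at any sample size, so recruiting more patients under the same rules would not help.

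**How far entrants' results fix the wider answer**

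Let s be the share of otherwise eligible patients who meet the digital criteria, and f the success share among entrants. If nothing is known about the excluded share, feasibility among all otherwise eligible patients lies between s × f (none of them would succeed) and s × f + (1 − s) (all would). The documents give neither s nor f. Both are assumed here, with f = 0.90.

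- s = 0.90: 0.81 to 0.81 + 0.10 = 0.91
- s = 0.70: 0.63 to 0.63 + 0.30 = 0.93
- s = 0.50: 0.45 to 0.45 + 0.50 = 0.95

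These bounds also assume that entrants represent everyone who meets the digital criteria. Refusal and convenience selection add uncertainty that the bounds do not include.

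**The case against.** The strongest reply is that a device with internet is a precondition for an app-delivered program. The aim is already confined to low-risk patients at one hospital, the study is called a pilot, and a later trial of the same app would need similar entry rules. All of that stands, and it is why the entry criteria should stay. It does not justify the wider wording of the barrier aim or of the section 3 conclusion.

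A second reply is that reasons for ineligibility and refusal may be recorded elsewhere. Section 2 commits to CONSORT and points to a SPIRIT checklist and a flow diagram, neither of which is shown. This also stands: the lack of a screening log in a condensed article is not an error. But the feasibility measure in Table 2 and the rule in section 3 use only entrants' data, and flow counts under convenience selection give no clear denominator of eligible patients.

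Some stronger readings are tempting but not supported:

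- *The trial misses the main barriers.* The article does not rank barriers or say how many patients lack access, and common usage barriers can be seen.
- *The adherence result will be wrong.* Adherence is sessions completed by users. Multiplying it by an assumed reach gives a different quantity and does not show an error in it.
- *The remark on few obstacles in section 4 is a claim about reach.* In context it compares hardware and software demands with those of other studies, and technical difficulties are acknowledged in the same section.
- *Convenience sampling contradicts the diversity statement in section 2.1.* Sampling described as intentional can deliberately seek diversity.

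**Conclusion.** The point holds in limited form. As described, the trial can identify common barriers of use among digitally equipped volunteers. It cannot show barriers of access, digital skill or refusal. The data therefore serve the implementation-barrier aim only in part, and the feasibility conclusion in section 3 goes beyond the patients studied.

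The size of the gap cannot be derived from the article. If nearly all otherwise eligible patients meet the digital criteria and accept, little is lost. If a substantial share do not, the entrants' result leaves the wider answer open over a broad range. The conclusion rests on the stated entry criteria, sampling method, source of barrier data and feasibility rule; it does not depend on the illustrative shares.

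**What to change.** 1. Keep the entry criteria.
2. In section 2.1, replace convenience selection with an approach to consecutive patients who meet all the non-digital criteria, made at the Stage 1 identification step already in section 2.4.
3. For each such patient not enrolled, tally the reason (no device or internet, unable to use messaging, technology-related exclusion, declined the app, other), and count these reasons in the barriers result.
4. Report reach, defined as enrolled divided by clinically eligible, alongside the feasibility outcomes in Table 2.
5. Restrict the section 3 conclusion to *feasibility in low-risk cardiac patients of this hospital with home internet access and digital skills*.
6. If consecutive screening is not done, restate the secondary aim in section 1 as *barriers of use among patients with digital access*.

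The cost is a short tally by staff who already identify candidates, plus wording changes. No extra patients, visits or procedures are needed. The downside is a narrower and less favourable feasibility statement.
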